### Patient inclusion criteria

Three groups of ‘high-risk’ patients will be included in the study:aged over 65 years;aged 18–65 years with common chronic and/or complex ACSC (chronic obstructive pulmonary disease (COPD), diabetes, angina (or ischaemic heart disease), cardiac failure, asthma); oraged less than 16 years and at risk of hospitalisation, defined by previous diagnosis with a high-risk condition (e.g. asthma, epilepsy, dental condition, acute bronchiolitis, pneumonia or croup).

### Patient recruit1ment

Following practice randomisation, in both intervention and control practices, an electronic database search will be conducted by the PN, PM or appropriate administrative staff member (assisted by a research team member, when necessary) using the practice’s own clinical software search facility to identify active patients (attended the practice three or more times in the last 2 years) who meet the inclusion criteria for the study.

Practices will generate lists of eligible patients seen by participating GPs, using 31st May 2018 as an index consultation day from which to extend searches. The generated lists will be screened by patients’ GPs to exclude patients unable to understand English or with significant cognitive impairment or distress. Then, the practice will post out a supplied information pack, consisting of a letter of invitation, an information sheet and a consent form, to a total of 200 eligible patients. This process will be the same in both the intervention and control groups. Information packs will be distributed to a sample of three patient cohorts from each practice, as follows:*n* = 60 patients aged over 65 years;n = 60 patients aged 18–65 years with chronic and/or complex ACSCs; and*n* = 80 parents of eligible children aged less than 16 years.

From the 200 information packs it is anticipated that, via an expected response rate of 25%, we can meet the target recruitment of 50 patients per practice. If recruitment is less than anticipated, a further wave of invitations will be sent and/or GPs can direct eligible patients to the trial information packs in each surgery. Patients’ consent to participate will be interpreted as the return of a completed consent form to the practice/the research team.

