### Randomisation of practices

We will use randomisation by minimisation to reduce the risk of the trial being unbalanced across arms by practice size (less than or equal to 5 full-time equivalent GPs, or 6 or more) and Index of Relative Socioeconomic Disadvantage (IRSD) at each practice’s local government area (whether in the most disadvantaged 40% or not, using Socio-Economic Indexes for Areas (SEIFA) [32]. Randomisation will be dynamic and conducted by the trial statistician ([name]) as practice level consent is obtained. The identity of the practices will be masked from the statistician until after the analyses are performed. The project officers in each state will enter a code for each consented practice into a cloud-based database in the order that the practice consents are received and notify the statistician by email. The statistician will then perform dynamic randomisation by minimisation, balancing for practice size and IRSD, entering the allocation into the database. With the exception of the statistician, all participants and project staff will be aware of the practice allocation to the control or intervention arms of the trial.

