**Fig. 2 Fig2:**
[figure not shown]
Plain language incentive structure (as provided to participating general practices)

An intervention facilitator (IF) will be employed by each of the three collaborating centres. They will work with practices in the intervention arm of the study to facilitate implementation of the new service model. They will also collect data relevant to their facilitator role using structured diary keeping. These diaries will contribute data concerning practice culture, communication and routines, plus information about the challenges and successes of the intervention. The EQuIP-GP Trial timeline is summarised in Table 2.

**Table 2 Tab2:** EQuIP-GP Trial timeline

Task Name	Start	Finish
*Practice Recruitment*	April 1 2018	November 30 2018
○ Publicity will be communicated through the PBRN newsletter and/or blog posts		
○ After publicity appears, all practices in the three PBRN’s will be sent a letter, information sheet and consent form.		
○ Practices expressing interest will receive a visit from investigators or a research staff team member to facilitate a more detailed discussion of the study.		
Practice Randomisation ○ Dynamic randomisation of practices will occur after consent has been gained by practices.		
Data collection ○ Distribution of pre-trial provider and facility surveys to practices		
○ A sample of consenting practice staff will be contacted directly by the research team to arrange qualitative interviews following randomisation		
*Patient Recruitment*	June 1 2018	December 31 2018
○ A Practice Nurse in the consenting practices will run an electronic search of the patient database in order to identify potential participants who meet the inclusion criteria		
○ A sample of 200 patients identified in the electronic search will be sent an information pack containing a letter of invitation, an information sheet and a consent form. ○ After 2 weeks, if recruitment is insufficient, then direct invitation to patients presenting to the practice will commence		
Baseline data collection ○ Distribution of pre-trial patient surveys: PCAT, EQ-5D-5 L HRQOL and ease of access survey to parents/guardians of <16 patients.		
○ A sample of consenting patients will be contacted directly by the research team to arrange qualitative interviews following recruitment.		
*Intervention period*	August 1 2018	July 31 2019
Intervention facilitation		
○ Intervention facilitators to visit intervention GP practices 3 times	August 1 2018	January 31 2019

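### Patients are listed, screened and topped up by staff who know the practice's arm, so the comparison is open to identification and recruitment bias

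*Protocol article*

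**What the plan says.** All references are to the Protocol article.

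- **Order.** The patient recruitment section states: "Following practice randomisation, in both intervention and control practices, an electronic database search will be conducted". The section on sample size and power gives the same order, with practices randomised first and patients recruited next.
- **Who knows the arm.** The section on randomisation of practices says that, apart from the statistician, "all participants and project staff will be aware of the practice allocation to the control or intervention arms of the trial".
- **Screening.** "The generated lists will be screened by patients’ GPs to exclude patients unable to understand English or with significant cognitive impairment or distress".
- **Invitation.** Each practice posts 200 packs in a 60/60/80 split across the three patient groups. A 25% response is expected to give 50 patients.
- **Top-up.** If recruitment falls short, the patient recruitment section allows a further wave of mailed invitations and/or a route in which "GPs can direct eligible patients to the trial information packs in each surgery". Table 2 words it differently: "After 2 weeks, if recruitment is insufficient, then direct invitation to patients presenting to the practice will commence".
- **Payment.** The intervention section bases incentives on the percentage change among a practice's enrolled patients, comparing the 12 trial months with the 12 months before.
- **Stated protections.** The process is to be the same in both arms, searches use a fixed index date of 31 May 2018, and eligibility criteria are identical. The primary outcome is a between-group difference in change in PCAT relational continuity, and prior prescription counts are used to adjust for case-mix.

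**The concern.** Cluster randomisation protects the comparison of practices. It protects the comparison of patients only if who enters each practice's sample does not depend on the arm. Here every step that shapes the sample follows randomisation and is in the hands of people described as aware of allocation. Two of those steps involve judgement: GP exclusion, which includes significant distress as a ground, and GP direction or direct invitation at the surgery.

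The motive is also one-sided, because only intervention practices are paid on change among those they enrol. The primary outcome is the patient's perceived relationship with the GP, and that same GP helps to decide who enters. The utilisation outcomes use the same comparison with the previous 12 months as the payment does. Patients enrolled after an unusually heavy year would tend to show a fall through regression to the mean, whether or not care had improved.

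At stake is whether a between-arm difference in the primary or utilisation outcomes can be attributed to the funding model. A larger sample would not help, because it reduces variance and leaves this bias unchanged.

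**Working it through.** **1. Sequence.** Put together, the sections read: practice consents, practice is randomised, arm is known to all but the statistician, practice staff run the search, GPs screen, packs are posted, and the shortfall is topped up. The article describes no step that hides the arm from those who search, screen or invite. Table 2 adds an overlap: patient recruitment and baseline surveys run from 1 June to 31 December 2018, while the intervention starts on 1 August 2018. Some baselines may therefore follow the start of implementation.

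**2. The plan's own figures.** Recruitment is consistent: 0.25 × 200 = 50 per practice, and 36 × 50 = 1800. The 98% power for a 0.2 change in adults cannot be reproduced, because the article gives no SD. It can be solved backwards, assuming a two-sided 5% test and 18 practices per arm:

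- adults per practice: 0.25 × (60 + 60) = 30
- design effect: 1 + 29 × 0.05 = 2.45
- effective n per arm: 18 × 30 / 2.45 = 220.4
- implied SE: 0.2 / (1.960 + 2.054) = 0.0498
- implied SD: 0.0498 / √(2/220.4) ≈ 0.52

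The power claim is not in dispute. The SE serves only as a yardstick below.

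**3. Level against change.** Let q be the between-arm difference in the share of patients who are selectively recruited.

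- If those patients differ from the rest by a stable amount L in PCAT *level*, the arms differ by qL at baseline and by qL at completion. The difference in change is qL − qL = 0.
- If they differ by D in expected PCAT *change*, the bias in the primary contrast is q × D.

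Only the second case matters for the primary contrast as written. A selected level matters only if it carries a different expected change, for example less room to rise on a scale with a maximum of 4.0.

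**4. Illustration.** The documents give neither q nor D. Assume q from 0.10 to 0.30 and D from 0.2 to 0.3. With bias b, the two-sided error is 1 − Φ(1.96 − b/SE) + Φ(−1.96 − b/SE).

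| q (assumed) | D (assumed) | bias b | share of 0.2 | error, nominal 5% |
|---|---|---|---|---|
| 0.10 | 0.2 | 0.02 | 10% | about 7% |
| 0.20 | 0.3 | 0.06 | 30% | about 23% |
| 0.30 | 0.3 | 0.09 | 45% | about 44% |

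These rows show sensitivity and are not estimates. The sign of D is open, so the bias could run either way.

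**5. The stated protections.** An identical procedure can still select differently when those applying it know the arm. The index date and electronic search fix the eligible pool, but not whom the GP removes or directs to a pack. Baseline measurement and prescription counts can adjust for what they measure. They do not capture motivation, attachment to the GP or capacity to change.

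**The case against.** The strongest defence is that discretion is narrow. The search is electronic, the index date is fixed, activity is defined by three or more visits in two years, the exclusions are named and the quotas are set. Top-up is conditional, and a further mailed wave is listed first. Case-mix is adjusted. All of this limits the room for selection and stands to that extent, but none of it blinds anyone.

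Other points carry weight:

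- The article does not say at what moment a practice learns its arm. It does place listing after randomisation and describes all but the statistician as aware, and it mentions no withholding.
- The two-week trigger stands in Table 2 without mention of GPs, and GP direction stands in the patient recruitment section without the two weeks. They should not be read as one rule.
- How the 200 are drawn is not stated. A condensed article may leave that to the full protocol, so the point does not rest on it.
- The incentive figure is not shown, so the motive rests on the text of the intervention section alone. The health economic section says the payment method guards against cream skimming, but it describes no control at the recruitment step.

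A reader might go further and infer that patients who present to intervention practices differ from those in control practices because of the longer or same-day appointments. The documents do not support that: the offer is made to patients already enrolled, so it does not explain who attends before enrolment.

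**Conclusion.** The point holds as a risk built into the design. Patients are identified, screened and topped up after randomisation by people who know the arm, and only one arm has a payment linked to change among those enrolled. The primary and utilisation comparisons are open to identification and recruitment bias that the stated protections reduce but do not fully remove.

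A reader might infer that the comparison is in fact biased, or biased in favour of the intervention. A protocol cannot show either. A reader might also size the bias from how much GP-directed patients differ in PCAT level. That does not carry over to a contrast in change, where a stable level difference cancels.

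Size and direction cannot be derived from the documents. The range of 0.02 to 0.09 rests wholly on assumed shares and assumed differences in expected change, and the error rates further assume a two-sided 5% test and the SE implied by 98% power.

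**What to change.** **Design.** Keep practice consent and minimisation, but tell each practice its arm only after three steps:

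1. the search at the 31 May 2018 index date has been run;
2. GP exclusions have been recorded and locked;
3. the 60/60/80 invitees have been drawn at random from the locked list, on coded IDs so that identifiable lists stay with the practice.

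Top up only through the further mailed wave that the plan already allows, drawn from the same locked list. Drop GP-directed and in-surgery invitation.

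**Cost.** Disclosure of allocation is delayed by a few weeks, and top-up may be slower.

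**This cohort.** The trial status section reports patient recruitment as completed on 31 December 2018, so the ordering can no longer be changed for these practices. What remains is to:

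- identify each patient's recruitment route;
- report the numbers listed, excluded by GPs, invited and consented, by arm;
- add a sensitivity analysis restricted to mailed-list patients.

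The report should say that this analysis addresses the top-up routes only. Mailed patients were also screened by their GPs after allocation, so any bias from that screening remains. The cost is mainly retrieving route and screening data from the practices.

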### Randomisation of practices

We will use randomisation by minimisation to reduce the risk of the trial being unbalanced across arms by practice size (less than or equal to 5 full-time equivalent GPs, or 6 or more) and Index of Relative Socioeconomic Disadvantage (IRSD) at each practice’s local government area (whether in the most disadvantaged 40% or not, using Socio-Economic Indexes for Areas (SEIFA) [32]. Randomisation will be dynamic and conducted by the trial statistician ([name]) as practice level consent is obtained. The identity of the practices will be masked from the statistician until after the analyses are performed. The project officers in each state will enter a code for each consented practice into a cloud-based database in the order that the practice consents are received and notify the statistician by email. The statistician will then perform dynamic randomisation by minimisation, balancing for practice size and IRSD, entering the allocation into the database. With the exception of the statistician, all participants and project staff will be aware of the practice allocation to the control or intervention arms of the trial.

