### Data management

On receipt of their consent forms, all participants (practice and patient) will be assigned a code, which will link their data to a master-sheet which will contain participants’ demographic details and location. The master-sheet will be kept secure and confidential by the project coordinator in a password-protected file in the project data management system. All data for the evaluation of the project will be identified by the participants’ code only. This is so that the data can be kept confidential, but can be re-identified to enable appropriate grouping and analysis in the case studies at the end of the study. As general practices will be involved in the extraction of their own consultation time and access data, data extraction will be performed by a staff member of the practice who has usual access to the data.

All participants (practices and patients) will have the choice of providing their data in hard copy or online data collection forms. We will use ‘CloudStor’ as a secure, password-protected, cloud-based data collection and storage facility for participant-provided project research data [38]. The CloudStor server for the project is located in Australia. Permission for access to the data within the research team will be an only-if-needed basis. Hard copies of all consent forms will be stored in locked filing cabinets in the Departments of General Practice at each respective university (or password-protected folder on CloudStor if in soft copy form).

After data integrity checks, data extracts received from MedicineInsight will be stored in CloudStor. Data collected from the MBS, PBS, hospitalisation and deaths registries will be collected for 5 years following the trial, but only with express consent from the participants. These data will be stored and analysed in the Secure Unified Research Environment (SURE) maintained by the SAX Institute [39]. SURE is a purpose-built remote-access data research laboratory and storage facility with servers located in Australia.

Interview and IF diary data will be stored securely at each site during the collection period.

De-identification will take place after transcription of interviews. The code sheets and de-identified transcripts will be stored separately in CloudStor.

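### The randomisation procedure masks practice identity, not trial arm, from the allocating statistician, so the sentence excepting the statistician from awareness of allocation is wrong as a statement of arm blinding

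*Protocol article*

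**What the plan says.** The protocol article deals with this in two sections.

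**Randomisation of practices.** The allocator is named by role: "Randomisation will be dynamic and conducted by the trial statistician". Practices reach that person under a code: "The project officers in each state will enter a code for each consented practice into a cloud-based database". The allocation step follows: "The statistician will then perform dynamic randomisation by minimisation, balancing for practice size and IRSD, entering the allocation into the database". Two statements on masking go with it. One concerns identity: "The identity of the practices will be masked from the statistician until after the analyses are performed". The other closes the section and concerns allocation: "With the exception of the statistician, all participants and project staff will be aware of the practice allocation to the control or intervention arms".

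**Data management.** Coding is described in general terms: "On receipt of their consent forms, all participants (practice and patient) will be assigned a code, which will link their data to a master-sheet". The master-sheet is kept by the project coordinator. On the evaluation data the section says: "All data for the evaluation of the project will be identified by the participants’ code only".

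The article does not say that codes are changed before analysis, that arm labels are hidden in the analysis file, or that someone other than the allocating statistician analyses the data.

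**The concern.** The one person said to be unaware of allocation is the person who produces and records it. Knowing an arm by practice code and knowing it by practice name are different things, and the procedure hides only the name.

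Choices made during analysis can be influenced by knowing which arm a record belongs to. The practice's name is not needed for that. Everyone else in the trial knows the allocation, and the primary outcome, relational continuity on the PCAT, is completed by patients. The statistician's unawareness is the only masking to arm that the article claims. Some discretion is left: the primary scale is identified only as the relevant one of a 43-item instrument, and there are many service-use outcomes. If the closing sentence is carried into the results paper as a blinded statistician, the procedure described here would not support it.

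**Working it through.** No sample size, power or error rate enters this point, and there is no figure to reproduce. The check sets the statements side by side.

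| Question | Answer in the article | Stated or inferred |
|---|---|---|
| Who runs the minimisation? | The trial statistician | Stated, Randomisation of practices |
| Who enters each arm into the database? | The same statistician | Stated, same section |
| What is hidden from that person? | Which practice lies behind a code | Stated, same section |
| Is the arm of a code hidden from that person? | It cannot be, because that person assigns it | Follows from the two allocation rows |
| Who analyses the data? | Apparently the same statistician | Inferred |
| Is the randomisation code the code in the analysis file? | Apparently | Inferred |

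**Step 1: arm by code.** The statistician assigns an arm to each code and types it in. Minimisation also uses the running balance of the arms on practice size and IRSD, so earlier assignments are in use at each later one. With 36 practices planned, the allocator would have generated 36 code-to-arm assignments. This follows from the stated procedure alone.

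**Step 2: what the masking covers.** Project officers supply codes, so the allocator need not know which practice a code stands for. This is feasible and consistent with Step 1. It protects identity and leaves the arm open.

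**Step 3: the closing sentence.** Read as unawareness of arm, it contradicts Step 1. Read as unawareness of which named practice is in which arm, it agrees with Step 2, but it then adds nothing to the identity sentence and is not arm blinding.

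**Step 4: from allocation to analysis.** For the analyst to know the arm of each record, two further links are needed.
- *The allocator analyses.* Identity stays masked until the analyses are finished. That limit has little purpose unless the statistician performs or directs them, and no other analyst is named. The analysis section does not say who does the work.
- *The codes carry through.* Practices receive a code at consent and the evaluation data are identified by participants' codes. The planned models have random effects at practice level, so the file needs a practice identifier. No sentence says that the code entered for randomisation is the one used in the data.

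Steps 1 to 3 rest on the text. Step 4 is a reasonable reading that the text does not confirm.

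**The case against.** The strongest reply is that the section describes real masking and the closing sentence should be read with it. Practices are coded, their identity is withheld until analysis is over, and the last sentence can mean that everyone except the statistician knows which actual practice is in which arm. This stands in part: identity masking is stated and workable. A reader might infer that the trial has no blinding at all, and the article does not support that. The reply does not rescue the sentence as a claim about arm, because the sentence speaks of allocation to control or intervention and will be read that way.

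A second reply is that the links in Step 4 are unstated, and that coding of the analysis file is the kind of detail left to a full protocol or SAP. This also stands. A reader might infer that the analyst is certain to know the arm of all 36 practices. The documents support that only for the allocator and only by code. The absence of a re-coding procedure is not itself the fault. The fault is a stated property that the stated procedure does not deliver.

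A third reply is that the analysis is already constrained: hierarchical models with practice-level random effects, prior prescription counts for case-mix, and no exclusion for non-adherence or protocol violation. This stands and narrows the room for arm-aware choices, exclusions in particular. It is also true that masking the statistician would not remove bias arising from patients knowing their arm.

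**Conclusion.** The point holds for the claim of arm blinding. The protocol article masks practice identity, not arm, from the statistician who allocates. The closing sentence of Randomisation of practices is wrong if taken to mean that this person does not know the arms. That much needs no assumption beyond the text.

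That the analysis is not arm-blind is conditional. It requires the allocating statistician to be the analyst and the randomisation codes to be those in the analysis file. Both are suggested and neither is stated. The size of any resulting bias cannot be worked out from the documents, and no direction can be given. The practical consequence is that the article does not justify reporting a blinded statistician.

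**What to change.** Moving the minimisation to someone else is no longer possible. The timeline ends practice recruitment on 30 November 2018, and Trial status reports patient recruitment complete and the intervention under way. Two options remain.

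1. **Make the analysis arm-masked.** The project coordinator, who already holds the master-sheet, issues the analysis file with fresh random practice codes and arms labelled A and B. The key stays closed until the primary analysis code is locked. The cost is one re-coding step by existing staff, with no further data or patients. The masking may be imperfect: the statistician knows the size-by-IRSD make-up of each arm from the minimisation, and both variables are listed in Table 3. These two binary factors give 2 × 2 = 4 cells. Any cell with an odd number of practices cannot split evenly, and such a difference could help show which label is which. The report should acknowledge this. The closing sentence should also be reworded to say that the allocating statistician knew arms by code and that the analysis file was re-coded.

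2. **Correct the claim.** Otherwise, reword the closing sentence to say that only practice identity is masked from the statistician, and do not describe the statistician as blinded in the results paper. This costs one sentence.

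If a separate analyst or a re-coding step is already in place, stating that in the same section would settle the Step 4 question. The closing sentence would still need correcting for the allocator.
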